## Abstract

**Introduction::**

The incidence of psoriasis vulgaris is increasing worldwide. Chronic recurrence of the disease, as well as accompanying cardiovascular disease, metabolic syndrome, and depression has affected the physical and mental health of these patients. Psoriasis vulgaris is a difficult and major disease in the dermatology field. Short-term curative effects using conventional therapy for psoriasis vulgaris has made major strides. However, traditional Chinese medicine (TCM) treatment has long-term curative advantages for psoriasis vulgaris but lacks the scientific and clinical evidence for its use. This study intends to demonstrate and provide scientific and clinical evidence for the use of TCM to delay the recurrence of psoriasis vulgaris.

**Methods and analysis::**

This will be a prospective, multicenter cohort study. We intend to recruit 1521 psoriasis vulgaris patients from 14 hospitals in Beijing, Tianjin, and Hebei. Treatment will be based on the diagnosis specifications and clinical practice guidelines of TCM and conventional therapy. During inclusion and the subsequent follow-up period, doctors through electronic case reports will collect different therapeutic TCM regimens and conventional therapy that were administered. Information on life condition, skin lesions at each visit, World Health Organization Quality of Life Instruments, Zung Self-rating Anxiety Scale, Zung Self-assessment of Depression, laboratory examinations, incidence of new rash and recurrence during the remission and recurrence stages will be recorded.

**Ethics and dissemination::**

The clinical trial protocol for this study was approved by the ethics committee of the Beijing hospital of TCM affiliated to capital medical university (Ethics number: 2019BL02-010-02). We will publish and present our results at national and international conferences and in peer-reviewed journals specialized in dermatology.

**Trial registration::**

This protocol has been registered in clinicaltrials. gov (ChiCTR1900021629)

## Introduction

1

Psoriasis is a common chronic, recurrent, immune-mediated dermatological disease. Environmental and genetic factors and their interactions are thought to contribute to the disease. Typical clinical manifestations are scaly erythema or plaques. They may be localized or present throughout the body. The disease is difficult to treat and often has lifetime risks. It affects about 3% of the worlds’ population, with a higher prevalence in Europe and the United States compared to China (0.123-0.47%). However, the incidence rates have been increasing over the years.^[1]^ Patients with psoriasis are usually accompanied with cardiovascular diseases, diabetes, metabolic syndromes, mental diseases and enteritis.^[2–4]^ It seriously affects the physical and mental health of patients and is a burden on medical resources. The 1-year recurrence rate of psoriasis is as high as 73.7%,^[5]^ and is a key concern for patients with psoriasis. High-risk factors for recurrence include tobacco use, alcohol, dampness, upper respiratory tract infections, certain medications, mental stress, being overweight and increased body fat ratios.

Conventional therapy that is used to treat psoriasis patients includes retinoic acid, phototherapy, immunosuppressive agents and targeted biological agents. However, these first-line therapies are expensive and have several adverse side effects.^[6,7]^ Previous studies have demonstrated that cyclosporin A, calcipotriol and methotrexate could moderately prolong psoriasis recurrence through sequential therapy, topical drug therapy, 308 excimer laser and biological agents .^[8]^ The majority of conventional therapies include a dosage reduction scheme, lifestyle changes and health education to delay recurrence. These include relaxation, behavioral changes, balanced diets, fish oils, and foods rich in n-3 fatty acid supplements, in addition to smoking and drinking cessation and the use of topical emollients.^[9–11]^ However, these measures do not prevent relapse. There is a critical need to find alternative therapies to prevent the recurrence of psoriasis. Latin American Clinical Practice Guidelines on the systemic treatment of psoriasis offers an updated therapeutic information and a reference for therapeutic decisions, with the main goal of improving patient care, controlling symptoms, and improving patients’ quality of life. However, it does not provide guidelines on how to prevent recurrence.^[12]^

Treatment of psoriasis using traditional Chinese medicine (TCM) has a long history. It has been shown to reduce recurrence and have long-term curative effects.^[13,14]^ TCM is considered as a supplement to achieve a healthy qi and improve immunity in the weak. It can alleviate clinical symptoms and improve cure rates. A qualitative study demonstrated that TCM treatment for psoriasis was safe and could prevent recurrence, however additional clinical studies were needed.^[15]^ Hence understanding TCM for the treatment of psoriasis vulgaris is the key to improving the short-term and long-term efficacy of psoriasis vulgaris. This study may provide evidence for determining the long-term curative effects of TCM for psoriasis vulgaris.

## Methods and analysis

2

### Study design

2.1

This is a prospective, multicenter cohort study. The study was initiated in July 2019 and will end in December 2021. We plan to recruit 1521 psoriasis vulgaris patients from 14 hospitals in Beijing, Tianjin and Hebei province. All patients will be given therapies based on TCM and Conventional therapy guidelines and then followed-up for 1 year. Prior to recruitment, each participating hospital should be required to obtain ethics approval. Each participating hospital will follow a standard set of procedures. The flow chart of the study is depicted in Figure 1.

**Figure 1 F1:**
[figure not shown]
Flow Chart of the Study. BSA = Psoriasis surface area score, PASI = Psoriasis area and disease severity index score, SAS = Zung self-rating Anxiety Scale, SDS = Zung self-assessment of depression, TCM = traditional Chinese Medicine, VAS = visual analog scale of Psoriasis skin itch score, WHOQOL-BREF = World Health Organization Quality of Life Instruments. This figure described the flow chart of the Study.

### Participants

2.3

#### Eligibility criteria

2.3.1

The Inclusion criteria are as follows:

(1)Conform to the diagnostic criteria of Western and Chinese medicine for psoriasis vulgaris.^[16–18]^(2)Study participants will not be selected or excluded until the required number of patients are met to ensure continuous enrollment.(3)Volunteered to participate in the case registration study and signed an informed consent.

The Exclusion criteria are as follows:

(1)Patients with a combination of pre-existing serious systemic diseases, such as cardiovascular, liver, kidney and hematopoietic disease or other primary diseases.(2)Severe mental illness.(3)Patients with poor compliance, inability to communicate and unable to complete the pre-designed registration information.

#### Patient cohort division

2.3.2

Patients received TCM will be classified as the TCM treatment cohort. The TCM treatment course should occupy more than half of the total course of treatment, with the following stratigies:

(1)oral herbal medicine once a day(2)external use of Chinese medicine ointment with the area of body surface area (BSA) greater than or equal to the 10% of patients’ total BSA(3)acupuncture treatment(4)external use of TCM bath.

Patients received Conventional therapy following guidelines will be classified as the Conventional therapy cohort. Conventional therapies includ: external use of drugs (Cuticle promoter and Exfoliator pledge agent, glucocorticoid, vitamin D3, vitamin A acid derivatives, immunomodulatory drugs, and so on), Internal use of drugs (antibiotics, retinoic acid, glucocorticoid and immunosuppressants, biological agents, and so on). The treatment course should occupy more than half of the total course of treatment, with the following strategies:

(1)oral use of chemical drugs(2)external use of chemical drugs ointment with the area of BSA greater than or equal to 10% of the total BSA(3)biological agents injection.

Those who meet the requirements of TCM and Conventional therapy cohort meanwhile will be classified as the integrated therapy cohort.

Study assistants will be responsible for the initial visit and follow-up of each patient. The data collection schedule is shown in Table 1.

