Patient management, collection, and analysis of medical data is the aim of the present clinical study. Management of chronic diseases will be investigated using this methodology. Patients will be initially registered using unique codes and then will undergo the relevant examinations based on an standard operation process to ensure consistency. Second, patients will be regularly evaluated for their disease condition by regular follow-up visits. If patients are unable to be physically present, they will be evaluated via online or telephone follow-ups. Third, doctors and patients will have direct access via Wechat IDs managed by research assistants. For common problems, the research assistants will communicate with patients via Wechat to improve patient compliance. Fourth, the database will be regularly checked. Patient treatment plans often change, so it is necessary to review and modify information regularly. Treatments will be evaluated for efficacy and actual benefits of TCM for chronic diseases. After platform establishment, enrollment of patients based on inclusion and exclusion criteria should be strictly followed. Based on preset objectives, there will be different research plans and corresponding statistical analysis required. It will be necessary to hold regular meetings to further develop the platform, share knowledge and data so that investigators can benefit from this platform.

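### Cohorts are assigned by the therapy that fills most of an undefined total course, so relapse and switching can influence which cohort a patient is counted in

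*Protocol article*

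**What the plan says.** The design is observational: "This is a prospective, multicenter cohort study" (section 2.1). The only cohort rule is in section 2.3.2.

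- TCM: "The TCM treatment course should occupy more than half of the total course of treatment, with the following stratigies".
- Conventional: "The treatment course should occupy more than half of the total course of treatment, with the following strategies".
- Integrated: "Those who meet the requirements of TCM and Conventional therapy cohort meanwhile will be classified as the integrated therapy cohort".

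The article does not say when the total course begins or ends. It does not fix the cohort at enrolment, at first prescription or at PASI75, and it has no rule for patients who switch. The words in section 2.10.4 about the time of enrolment concern baseline comparability, not cohort assignment.

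Treatment is expected to change and is recorded over time. The abstract says: "During inclusion and the subsequent follow-up period, doctors through electronic case reports will collect different therapeutic TCM regimens and conventional therapy". The Discussion adds: "Patient treatment plans often change, so it is necessary to review and modify information regularly". The primary outcome (section 2.5.1) is 6-month recurrence in patients who have reached PASI75.

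On phototherapy, the Introduction says: "Conventional therapy that is used to treat psoriasis patients includes retinoic acid, phototherapy, immunosuppressive agents and targeted biological agents". None of the three qualifying conventional strategies in section 2.3.2 (oral drugs, ointment over a minimum area, biologic injection) covers it.

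**The concern.** A share of a total course can be computed only when the course is over. If the course runs past PASI75, it can contain treatment that was changed because the patient relapsed. Someone who relapses early on TCM and spends the rest of the course on conventional drugs is then counted as conventional and takes the relapse into that cohort. A switch the other way does the opposite. If relapsers add the second therapy instead of replacing the first, they move into the integrated cohort.

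In each case the label is partly a consequence of the primary outcome. Propensity score matching (section 2.10.5) and Cox adjustment for baseline PASI, disease course and body mass index (section 2.10.2) balance characteristics that exist before treatment. They cannot repair a label formed afterwards. At stake is who belongs to each group in the main comparison.

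The phototherapy gap is a smaller problem of the same kind. A patient on qualifying TCM plus phototherapy would count as pure TCM, although the Introduction treats phototherapy as conventional.

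**Working it through.** **The plan's own figure.** Section 2.7 assumes recurrence of 73.7% (conventional), 28.6% (integrated) and 20% (TCM), with α = 0.05 and power 0.8. A two-sided comparison of 28.6% with 20% (pooled variance, no continuity correction) needs 390 per group, which matches the plan. The study is therefore sized on TCM v integrated, a difference of 28.6 − 20 = 8.6 points. The planned TCM v conventional difference is 73.7 − 20 = 53.7 points.

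**Illustrative switching model.** The 28.6% is borrowed from section 2.7; every other input is an assumption.

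- Half of patients start each therapy, and true 6-month recurrence after PASI75 is p = 0.286 in both, with constant hazard.
- PASI75 is reached at month 2 and the course lasts 12 months.
- At relapse, a fraction sT of TCM starters and sC of conventional starters switch.

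A switch changes the majority therapy only before month 6, that is, within 4 months of PASI75. The probability of relapse in that window is

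q = 1 − (1 − 0.286)^(4/6) = 0.201.

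Per starter, the net outflow of relapsers from the TCM label is d = (sT − sC)q. Labelled recurrence is

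- TCM: (p − d)/(1 − d)
- conventional: (p + d)/(1 + d)

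| sT / sC | d | TCM | Conventional | False gap |
|---|---|---|---|---|
| 30% / 10% | 0.040 | 25.6% | 31.4% | 5.8 points |
| 50% / 10% | 0.080 | 22.4% | 33.9% | 11.6 points |
| 10% / 50% | −0.080 | 33.9% | 22.4% | 11.6 points, reversed |
| 30% / 30% | 0 | 28.6% | 28.6% | none |

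Classified by starting therapy, both groups show 28.6% in every row.

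**Timing, at 50% / 10%.**

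- PASI75 at month 4: the window is 2 months, q = 1 − 0.714^(2/6) = 0.106, giving 25.4% v 31.5%, about 6 points.
- PASI75 at month 6: the window is zero, giving 28.6% v 28.6%.
- A 6-month course with PASI75 at month 2: the window is 1 month, q = 1 − 0.714^(1/6) = 0.055, giving 27.0% v 30.1%, about 3 points.

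**Unequal true risks.** Take 20% and 73.7% as 6-month risks, with PASI75 at month 2 and a 12-month course. Then qT = 1 − 0.8^(4/6) = 0.138 and qC = 1 − 0.263^(4/6) = 0.590. With e = sC·qC − sT·qT, labelled recurrence is (0.20 + e)/(1 + e) for TCM and (0.737 − e)/(1 − e) for conventional.

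- 30% / 10%: 21.4% v 73.2%
- 50% / 10%: 19.2% v 74.0%
- 30% / 30%: 29.5% v 69.6%

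**Relapsers who add the other therapy.** A separate simulation assumed 50% true recurrence, PASI75 at 1 to 4 months, relapse uniform over the next 6 months and a 12-month course. With 30% of relapsers adding in each group, it gave TCM 45.3%, conventional 45.2% and integrated 100%. The 100% arises because nobody in that model starts on both therapies.

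A less extreme version uses equal thirds starting on each regimen, 28.6% true risk in all three, and the month-2, 12-month setting. With 30% adding, 0.3 × 0.201 = 0.060 of each single-therapy group moves to integrated:

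- TCM: (0.286 − 0.060)/(1 − 0.060) = 24.0%
- integrated: (0.286 + 2 × 0.060)/(1 + 2 × 0.060) = 36.3%

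**The case against.** The strongest reply is that the article never says the total course includes treatment after relapse. Section 2.1 can be read as separating the two phases: "All patients will be given therapies based on TCM and Conventional therapy guidelines and then followed-up for 1 year". Section 2.5.2 also names treatment and follow-up as distinct periods. If the course ends at PASI75, a later relapse cannot change the label. This stands as a limit on the claim. It does not remove the problem, because the article does not state that reading, treatment is recorded through follow-up, and switching before PASI75 would still shape the cohorts. The full protocol may define the term, but the rule as published leaves it open.

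Three stronger readings are tempting and not supported.

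- **That the false gap exceeds the difference the study is sized on.** The 8.6 points are TCM v integrated, whereas the switching model compares TCM with conventional, where the planned gap is 53.7 points. With the planned risks, the 30% / 10% and 50% / 10% patterns move either rate by less than 2 points.
- **That the bias vanishes only when switching is symmetric.** It also vanishes under asymmetric switching if PASI75 comes at month 6. Symmetric 30% / 30% switching with unequal risks does bias, towards the null.
- **That the rule favours TCM.** Reversed switching rates reverse the gap, and the article gives no rates.

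On phototherapy, the Introduction is background, and section 2.5.2 costs physical therapy separately from both TCM and conventional therapy, so it may be meant as a background modality. That makes the point secondary; the mismatch remains.

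**Conclusion.** The concern holds in this form: the stated rule classifies patients on information that arises after baseline, over a window that is not defined. Unless that window closes before PASI75, the primary outcome can influence cohort membership, and baseline adjustment cannot undo it.

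The size is not known. Under equal true risks and the assumptions above, the false TCM v conventional gap runs from none to about 12 points in either direction, depending on who switches, when PASI75 is reached and how long the course lasts. If relapsers add the other therapy, they collect in the integrated cohort and distort the TCM v integrated contrast, by an amount that again rests on an assumed rate. With no switching or adding, there is no bias from this source.

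The change should be made before analysis because it concerns group membership in the main comparison and is mainly a matter of wording. The phototherapy inconsistency is real but secondary, and its effect cannot be sized from the document.

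**What to change.** Define the cohort before the outcome clock starts.

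1. For onset time, safety and cost, use the regimen started at enrolment.
2. For recurrence and maintenance time, use the regimen that filled more than half of the period from enrolment to PASI75, and integrated if both did. Freeze the label at PASI75. This also gives a rule for patients who change regimen before PASI75.
3. Report later switches and additions by cohort.
4. Keep the total-course majority rule only as a sensitivity analysis, with the start and end of the course stated.
5. Reconcile the Introduction with section 2.3.2 on whether phototherapy counts as conventional exposure. This concerns classification for analysis only, not which treatment patients receive.

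The cost is protocol and analysis-plan wording, with no extra patients. The rule needs start and stop dates for each regimen. The article says regimens are recorded, but Table 1 is not available here, so the sponsor should confirm that dates are captured. Two cohort definitions will be in use across endpoints and need clear labels. A small downside is that some patients are analysed under a treatment they later left.

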**Table 1 T1:**
[figure not shown]
Data collection schedule.

### Ethical approval

2.4

This study has been registered in clinicaltrials.gov (registration number ChiCTR1900021629) and was approved by the ethics committee of Beijing Hospital of TCM, Capital Medical University (Approval number 2019BL02-010-02). Patients who met the inclusion criteria will be enrolled after obtaining signed informed consent.

### Outcomes

2.5

#### Main outcomes

2.5.1

Recurrence rate in 6 months. Definition of recurrence: Patients have got relief psoriasis area and disease severity index score (PASI75), while the total PASI score increased to 50% of the original PASI.^[19]^

#### Secondary outcomes

2.5.2

(1)Onset time: required time for 75% improvement of PASI scores(2)Maintenance time: the time from improvement (PASI75) to recurrence (PASI50)(3)BSA score: The patient's palm area equivalent to 1% of the BSA(4)Visual analog scale of Psoriasis skin itch score (VAS) score: Urticant degree “0 minutes” represents “do not have urticant feeling”, increase in urticant gradually increased score values. 10 minutes represents “the most serious urticant score”.(5)Skin relapse during treatment and follow-up period: The location of new skin lesions (head/trunk/arm/leg), number (1–2/3–5/6–10/>10) and new attack after 6-month interval (no attack/once, between 2-weeks to 1 month/once, every month to 2 months/once, every 2 to 3 months/once, every 3 to 4 months/once, after more than 5 months).(6)World Health Organization Quality of Life Instruments, which included the 28 items, with full credit of 100(7)Zung self-assessment of Depression, Depression was classified as either mild, moderate or severe.(8)Zung self-rating Anxiety Scale (SAS), Anxiety level was classified as either mild, moderate or severe.(9)The total score of the TCM clinical syndrome scale was calculated using blood heat syndrome, blood dryness syndrome and blood stasis syndrome.(10)Treatment expenses (The cost of registration, TCM, Conventional therapy, examinations, physical therapy, acupuncture, transportation expenses, accommodation, and other expenses)

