#### Non regulatory analysis

2.10.2

For the comparative analysis of 2 groups, qualitative data will be analyzed using the chi-square test, Fisher exact probability, Wilcoxon rank-sum test and CMH chi-square test. Quantitative data in line with normal distribution will be analyzed using *t*-test (homogeneity test of variance between groups, test level at 0.05, and Satterthwaite method will be used for correction when the variance is uneven). Wilcoxon rank-sum test and Wilcoxon signed-rank sum test will be used when the data is abnormally distributed.

The survival analysis will be used to compare statistical significance between the groups (for the appearance of new skin lesions). In addition, the Cox regression model will be used to adjust the impact of baseline PASI values, course of the disease, and body mass index.

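### The printed levels for the interval between new attacks are not exhaustive: intervals above 4 and up to 5 months, and under 2 weeks, have no code, and some boundaries are coded twice

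*Protocol article*

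**What the plan says.** Item (5) of section 2.5.2 in the protocol article is headed "Skin relapse during treatment and follow-up period". It has three components: the site of new lesions, their number, and how often new attacks occur. The third component opens with "new attack after 6-month interval (no attack/once, between 2-weeks to 1 month/once", continues with "every month to 2 months/once, every 2 to 3 months/once, every 3 to 4 months/once", and closes with "every 3 to 4 months/once, after more than 5 months".

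Read as a scale, the levels are: none; 2 weeks to 1 month; 1 to 2 months; 2 to 3 months; 3 to 4 months; more than 5 months. No residual level such as other or unknown is printed, and no other section adds one.

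Two further places bear on the item. Section 2.1 says that patients will be "followed-up for 1 year", so intervals of four months and longer can be observed. Section 2.10.2 plans a survival analysis "for the appearance of new skin lesions" with Cox adjustment, but does not say whether it uses these levels or dates.

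**The concern.** A coded outcome needs levels that cover every possible value, each once. This list is contiguous from 2 weeks to 4 months, jumps to more than 5 months, and has nothing at the short end below 2 weeks. Whoever codes a patient with a 4.5-month interval has no correct choice: the field stays empty, or the patient goes into 3–4 months or more than 5 months.

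The lesion-count component of the same item has no such break (1–2, 3–5, 6–10, more than 10). That suggests the break is a slip and not a decision to leave out part of the range.

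What is at stake is whether this component can be interpreted. The study asks whether treatment delays recurrence, and the Discussion expects some patients to recur early and often and others to stay in remission for long. Information at both ends of an interval scale is therefore wanted.

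**Working it through.** The document states no figure to reproduce; the check is whether each possible interval falls in exactly one level.

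**Inputs.** The printed levels from section 2.5.2, item (5), expressed in months. Two weeks = 14 / 30.44 = 0.46 month. End points are taken as inclusive, since the text assigns them to neither side. The levels are then [0.46, 1], [1, 2], [2, 3], [3, 4] and more than 5.

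**Levels containing each test value:**

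| Interval (months) | Number of levels that fit |
|---|---|
| 0.25 | 0 |
| 0.40 | 0 |
| 0.5 | 1 |
| 1.0 | 2 |
| 1.5 | 1 |
| 2.0 | 2 |
| 3.0 | 2 |
| 4.0 | 1 |
| 4.3 | 0 |
| 4.5 | 0 |
| 5.0 | 0 |
| 5.2 | 1 |

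Exactly 5 months also has no level, because the last one starts above 5.

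**Does the result depend on how the string is parsed?** The slashes and commas can be read in two ways: the word once may begin each level or belong to the phrase before it. The opening, "no attack/once, between 2-weeks to 1 month/once, every month to 2 months", shows the ambiguity. Both readings give the same end points, so both leave the same two gaps.

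**Width of the gaps.** Below 2 weeks: 0.46 month. Above 4 and up to 5 months: 1.00 month. Total 0.46 + 1.00 = 1.46 months, and 1.46 / 6 = 24% of the first 6 months. This is a share of the time axis only.

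**Can it be turned into a share of patients?** Only by assuming a distribution. Suppose a single relapse time with constant hazard and 6-month risk p. The share of relapses at 4–5 months is [(1−p)^(4/6) − (1−p)^(5/6)] / p, and the share before 0.5 month is [1 − (1−p)^(0.5/6)] / p.

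- p = 0.286: 15.3% + 9.7% = 25.0%.
- p = 0.737: 11.1% + 14.3% = 25.4%.
- The Introduction calls 73.7% a 1-year rate. At constant hazard the 6-month risk is 1 − √(1 − 0.737) = 0.487, which gives 13.9% + 11.1% = 25.0%.

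The total is stable because it mostly reflects the width of the gaps (24% of the range) under a smooth curve. It is not evidence about this population, for the reasons given under the verdict.

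**The case against.** The strongest reply has four parts.

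1. **The article is a condensed text in rough English.** The phrase that introduces the levels, with its 6-month interval, is itself unclear, and the itch scale in the same section is given in minutes. The case report form is not shown, and more than 5 months may be a slip for more than 4. This stands as a caution about what staff actually see on the form. It does not remove the point: the article prints a specific list as the levels, and that list has a hole. If it is a slip, it still has to be corrected.

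2. **Two weeks may be a deliberate minimum.** Lesions appearing sooner could be regarded as part of the same flare. The document neither states nor excludes such a rule, so the lower gap is less certain than the upper one. The gap above 4 and up to 5 months does not depend on this.

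3. **The planned survival analysis needs event timing, not these codes.** If dates are recorded, that analysis is unaffected and the levels could be rebuilt from them. This stands, but the coded component remains defective as printed.

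4. **The consequence is small.** The item is one of ten secondary outcomes and the interval is one of its three components. This stands fully.

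**Conclusion.** The point holds as a gap in a category list. As printed, an interval above 4 and up to 5 months has no level, an interval under 2 weeks has none unless 2 weeks is meant as a minimum, and exactly 1, 2 or 3 months fits two levels. The upper gap is unambiguous. This is a minor matter. The primary outcome (section 2.5.1) is defined by PASI, the sample size (section 2.7) rests on recurrence rates, and neither uses these levels.

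Two stronger readings are tempting, and the document supports neither.

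- **A reader might infer that about a quarter of relapsing patients would have no valid code.** The document gives no distribution of attack intervals. The constant-hazard figures model time to a single event, whereas most of the levels describe how often attacks recur. The rates put in are those used in section 2.7 for PASI-defined recurrence, a different event from new lesions, and 73.7% is a 1-year rate in the Introduction. The share affected cannot be derived.
- **A reader might infer that the miscoding would bias the comparison between cohorts.** It could fall unequally if cohorts relapse at different speeds, but no section names a between-cohort analysis of these levels, and their distribution by cohort is unknown. This remains conjecture.

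**What to change.** Print levels that are exhaustive and do not overlap, with each boundary assigned once: none; under 2 weeks; 2 weeks to <1 month; 1 to <2; 2 to <3; 3 to <4; 4 to <5; 5 months or more. If 2 weeks is intended as the minimum separation for a new attack, say so in place of the under-2-weeks level. Alternatively, derive the levels from attack dates where these are recorded, which makes the boundaries a programming matter.

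The cost is an edit to the case report form and to the outcome text. Section 2.1 gives July 2019 as the start, so some records may already carry the printed levels. These can be re-coded only where dates were kept. Under section 2.8 a submitted page must be returned before it can be modified, with the change traced. Records without dates should be reported under the levels in force when they were entered.
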